## Methods

### Design

The study is a case-control study, including the baseline sample of 140 adults diagnosed with ASC enrolled in a randomised clinical trial [39] and a neurotypical control group of 50 adult individuals matched on age and sex. Participants will undergo a VR-based eye-tracking paradigm, wherein they will be presented with computer-generated stimuli within the *head-mounted display* (HMD). Gaze behaviour will be measured through eye-tracking technology integrated within the HMD. The study will employ a mixed-factorial design, featuring both within- and between-subject analyses.

### Data management, safety consideration and ethics approval

The study will be conducted in accordance with the Helsinki Declaration and following the guidelines of the Danish Committee on Health Research Ethics. In compliance with the Data Protection Act and the Data Protection Regulation, patient information will only be collected with the individual’s consent. All participants will be provided with written and oral information. Written, informed consent is required for all the participants. Participants may at any time retract their consent without consequences. Electronic data from psychometric assessments will be stored pseudo-anonymized in the REDcap database, an online electronic data capture tool, meeting the requirements of the Danish Data Protection Agency. Eye-movement data will be stored pseudonymised in logged folders on network drives under the control of the Capital Region of Denmark, CIMT. Physical media, including consent forms, will be stored locally and securely. Virtual reality is generally well tolerated, with minimal side effects or adverse events [40]. Side effects may include experiences of cybersickness following time in VR [41]. Side effects and adverse events will be monitored and recorded throughout the study. The study is registered at the Danish Data Protection Agency (p-2023–14488) and has been approved by the National Committee on Health Research Ethics in the Capital Region of Denmark (H-23055504).

### Setting

The study will be conducted by VIRTU Research Group at Mental Health Center Copenhagen, Copenhagen University Hospital, Denmark. Participants in the ASC group will be recruited from public and private outpatient diagnostic facilities in Denmark, specialised in the clinical assessment of ASC in adulthood, as well as from community-based social support services in the Capital Region of Denmark, provided they have a documented ASC diagnosis based on specialised clinical evaluation.

### Participants

#### Autism spectrum condition participants.

A total of 140 autistic adults (ICD-10 F84; 84.1; 84.5; 84.8) will be included.

Inclusion criteria for the ASC group are as follows: (i) primary diagnosis of autism (ICD-10 F84; 84.1;84.5;84.8), (ii) age ≥  18 years, (iii) a T-score on the SRS-A self-report of 60 or above, corresponding to 1 standard deviation above the general population mean, indicating clinically significant, mild to moderate difficulties with social interactions in daily life [42].

Exclusion criteria for the ASC group are as follows: (i) rejecting informed consent, (ii) a diagnosis of organic brain disease (ICD-10 F00 - F09), (iii) intellectual disability (IQ <  70), (iv) an insufficient command of spoken Danish or English, (v) an ADHD-diagnosis with medically untreated symptoms. ADHD symptoms are considered medically treated when participants demonstrate a satisfactory treatment response, as confirmed by their physician responsible for treatment. Additionally, participants must have no changes to dosage or type of medication within the preceding four weeks of study participation. This criterion aims to mitigate confounding influences and aligns with research indicating that medication-naïve adults with ADHD perform significantly worse than neurotypical controls on measures of visual attention, but that performance improves following six weeks of titrated methylphenidate treatment, including a two-week stable ‘end-point’ dosage [43]. Given the high rate of psychiatric co-occurrence often present among individuals with ASC, co-occurring disorders will not constitute an exclusion criterion in the ASC group, apart from co-occurring ADHD with medically untreated symptoms [44,45].

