Diagnosis in adulthood presents unique challenges. As a neurodevelopmental condition, ASC requires that symptoms be present from childhood, meaning diagnosis is contingent on accurate retrospective reporting, often from family members, which may neither be accurate nor accessible [13]. Additionally, many individuals who remain undiagnosed into adulthood do so as a result of acquiring compensatory strategies or camouflaging behaviours to mask their autistic traits in social settings, further complicating diagnostic processes [13,14]. Current diagnostic methods are also reliant on subjective measures such as self-reports and clinical observations, which may be susceptible to bias, potentially leading to misdiagnosis [15]. Objective behavioural markers, such as gaze behaviour, may have the potential to support current clinical assessment methods for ASC.

Gaze behaviour provides a valuable behavioural measure in understanding social cognition. The development of eye-tracking technology has enabled the quantification of gaze patterns, and the study of how individuals allocate visual attention. In humans, gaze functions as a signal to modulate communication, evident in the attentional bias known as *visual social allocation*, where neurotypical populations tend to direct attention towards socially salient features, such as eyes and faces [16,17]. Conversely, atypical gaze patterns may indicate aberrant social perception, reflected as impairments in social communication. As such, gaze behaviour may offer insights into assessing psychiatric conditions in which social communicative difficulties are present, such as ASC. The study of gaze behaviour in psychiatric populations has gained increasing attention in recent years, with studies examining its role in understanding various conditions, including ASC, social phobia, affective disorders and schizophrenia [18–22].

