#### Neurotypical participants.

Fifty neurotypical participants will be recruited from the community, using advertisements at relevant institutions or through the websites www.forskningnu.dk and www.forsoegsperson.dk.

Inclusion criteria for the neurotypical group are as follows: (1) age ≥  18 years, (2) ability to give informed consent.

Exclusion criteria for the neurotypical control group are as follows: (1) any current psychiatric diagnoses, including alcohol and drug dependence, (2) an insufficient command of spoken Danish or English. Neurotypical participants will be matched to the ASC sample on age (+/- 2 years) and sex.

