### Clinical

Mini International Neuropsychiatric Interview (M.I.N.I), v. 5.0 will be used to assess general psychopathology in order to record any cooccurring psychiatric conditions within the ASC group and to exclude any current psychiatric diagnoses within the neurotypical group [50].Danish Weschler Adult Intelligence Scale (WAIS-IV), subtests Vocabulary and Matrix reasoning, will be used to estimate full-scale IQ to confirm eligibility, which are known to correlate with full-scale IQ [51,52].Social Responsiveness Scale 2 – Adult Version, Self-report (SRS-2A Self-report), will be used to measure degree of social impairment [42].Social Responsiveness Scale 2 – Adult Version, Informant (SRS-2A Informant) will be used to measure degree of impairment as reported by an informant close to the participant [42]- Social Interaction Anxiety Scale (SIAS) [53] will be used to measure levels of social anxiety.Empathy Quotient (EQ) will be used to measure level of empathy [54].- Camouflaging Autistic Traits Questionnaire (CAT-Q) will be used to measure social camouflaging behaviours [12].- Sensory Reactivity in Autism Spectrum questionnaire (SR-AS) will be used to assess degree of sensory reactivity, including both hyperreactivity and hyporeactivity [55].Beck Depression Inventory (BDI) will be used to assess level of depressive symptoms [56].Repetitive Behaviour Questionnaire (RBQ-3) will be used to assess repetitive behaviours, including motor stereotypies, ritualistic behaviours and restricted interests [57].- Adult ADHD Self-Report Scale (ASRS) will be used to assess the severity of ADHD symptomology, including impulsivity-hyperactivity and inattention. [58]

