## Discussion

The proposed study aims to examine gaze behaviour differences between autistic adults and neurotypical controls using a VR-based eye-tracking paradigm. By investigating gaze behaviour within immersive, socially complex scenarios, this study aims to identify behavioural markers of ASC, which may hold clinical significance. Given that gaze abnormalities constitute a core feature of the clinical presentation of ASC [1], and are associated with difficulties in social communication and interaction, the findings from this study could expand on the current understanding of underlying social-cognitive deficits in ASC. The results may serve as the foundation for future studies investigating VR-based eye-tracking as an objective, non-invasive tool for assessing visual social attention in ASC.

A significant clinical implication of this research is the potential for developing objective assessment tools to aid in the clinical assessment of ASC. Eye-tracking technology, when integrated with VR, may offer an enhanced, ecologically valid method for evaluating gaze behaviour in real-world social contexts, thereby supporting current clinical assessment methods [20,37,38]. Although there are existing tools to evaluate social deficits in ASC, such as standardised behavioural assessments, these often rely on subjective clinician observations or self-report measures. VR-based eye-tracking offers the opportunity to observe gaze behaviour in a controlled, ecologically valid environment, providing data that may supplement existing diagnostic procedures.

Aberrant gaze patterns have been observed in a range of psychiatric conditions, such as affective disorders and schizophrenia [21,22,67]. As the current study focuses exclusively on an ASC population, future research may examine whether specific gaze patterns are unique to ASC or may be shared across clinical populations.

While VR technology is increasingly employed in therapeutic interventions [41,49,68,69], its use as a diagnostic or assessment tool remains relatively underexplored [70]. By measuring gaze behaviour in VR-based paradigms, this study may contribute to the potential utility of VR as an instrument when assessing psychopathology. Findings may also have therapeutic implications if distinct gaze patterns are identified within the ASC group, where gaze avoidance may become focal points for therapeutic interventions.

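### Co-occurring psychiatric disorders are admitted in the ASC group and excluded in controls, so the group contrast stands as a description but reading it as a gaze marker of autism is confounded

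*Protocol article*

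**What the plan says.** The eligibility criteria treat current psychiatric disorder differently in the two groups. For the ASC group (Participants, Autism spectrum condition participants), "co-occurring disorders will not constitute an exclusion criterion in the ASC group, apart from co-occurring ADHD with medically untreated symptoms". Organic brain disease and IQ below 70 are excluded separately. The reason given is "Given the high rate of psychiatric co-occurrence often present among individuals with ASC". For controls (Neurotypical participants), an exclusion criterion is "any current psychiatric diagnoses, including alcohol and drug dependence". The two groups are aligned on two variables only: "Neurotypical participants will be matched to the ASC sample on age (+/- 2 years) and sex".

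The Discussion states: "Aberrant gaze patterns have been observed in a range of psychiatric conditions, such as affective disorders and schizophrenia". The Introduction lists the conditions in which gaze has been studied, "including ASC, social phobia, affective disorders and schizophrenia".

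The M.I.N.I. is used "to record any cooccurring psychiatric conditions within the ASC group and to exclude any current psychiatric diagnoses within the neurotypical group" (Assessment battery, Clinical). Social anxiety (SIAS) and depression (BDI) scores are collected as well. Under Statistical analyses, the only covariate named for the gaze models is the ASRS score, included because of possible confounding by ADHD symptoms. The clinical measures otherwise enter a descriptive one-way ANOVA between groups and exploratory regressions on the eye-movement data.

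The Aim section asks whether gaze differs between autistic and neurotypical adults. The Discussion goes further and presents the study as a search for gaze markers of autism that could support clinical assessment.

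**The concern.** Group membership is tied by design to a second characteristic. Current psychiatric disorder is absent from the control group and, by the protocol's own account, common in the ASC group. The protocol also reports that some of these disorders go together with atypical gaze. A difference in eye dwell time can therefore come from autism, from co-occurring disorder, or from both, and the planned contrast does not separate them.

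The protocol accepts this reasoning for ADHD, where it uses both an exclusion criterion and a covariate. It states no counterpart in the gaze contrast for the affective and psychotic disorders that it links to atypical gaze itself. What is at stake is interpretation: a difference arising partly from mood or psychotic disorder could be reported as a marker of autism and carried into work on diagnostic tools.

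**Working it through.** **1. The plan's own figure.** Inputs from Sample size calculation: g = 0.47, SD = 1, two-sided alpha 0.05, power 80%, control-to-ASC ratio 0.35.

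- (1.960 + 0.842)² / 0.47² = 7.85 / 0.2209 = 35.53
- ASC: 35.53 × (1 + 1/0.35) = 137.05, which rounds up to 138 (stated: 139)
- Controls: 35.53 × 1.35 = 47.97, which rounds up to 48 (stated: 48)

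The figure reproduces. Non-central t power is 79.8% at 139/48 and 81.0% at the planned 140/50. The sample size is not in dispute; it supplies the scale for what follows.

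**2. What the documents give on the confounder.** They call co-occurrence frequent but give no rate. They say atypical gaze is observed in affective disorders and schizophrenia but give no effect size and no direction. The bias therefore cannot be computed from the documents.

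**3. Illustration with assumed inputs.** Let p be the share of the ASC group with a current co-occurring disorder, and d the shift in eye dwell time that goes with it, in SD and in the hypothesised direction. If autism itself has no effect, the expected group difference is p × d. The chance of p < 0.05 is the non-central t power at 140 vs 50.

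| p (assumed) | d (assumed) | p × d | chance of p < 0.05 |
|---|---|---|---|
| 0.3 | 0.3 | 0.09 | 8.4% |
| 0.5 | 0.3 | 0.15 | 14.8% |
| 0.5 | 0.5 | 0.25 | 32.7% |
| 0.7 | 0.5 | 0.35 | 56.1% |

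Without any such shift the chance would be 5%. A shift in the opposite direction would hide a real difference instead.

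**4. Could co-occurring disorder produce the whole planning effect?** The required shift is d = 0.47 / p: 1.57 SD at p = 0.3, 0.94 SD at p = 0.5 and 0.67 SD at p = 0.7. All lie above the range assumed in step 3.

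**5. Precision of a restricted comparison.** ASC participants without a current co-occurring disorder number n₁ = 140 × (1 − p). The unadjusted 95% CI half-width, in SD, is 1.96 × √(1/n₁ + 1/50).

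| ASC participants | n₁ | half-width | power at g = 0.47 |
|---|---|---|---|
| all | 140 | 0.32 | 81% |
| p = 0.3 | 98 | 0.34 | 77% |
| p = 0.5 | 70 | 0.36 | 71% |
| p = 0.7 | 42 | 0.41 | 60% |

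**The case against.** The strongest reply is that the stated question is answerable as designed. The Introduction defines neurotypical as having no developmental or current psychiatric diagnosis, so excluding diagnosed controls implements the comparison in the Aim section. Hypotheses 1-3 predict how the two groups differ and make no causal claim. This stands, and a reader who infers that the study cannot meet its aim, or that the hypotheses themselves attribute the difference to autism, goes beyond the text. The difficulty begins with the Discussion's step to markers of autism.

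Three other strong readings also fail:

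- **That the protocol says these disorders alter gaze.** It says atypical patterns have been observed in affective disorders and schizophrenia, which is association. Social phobia is named only as a condition in which gaze has been studied, and substance dependence is not linked to gaze at all. Association is still enough to make attribution unsafe.
- **That the comorbidity data go unused.** SIAS and BDI enter the descriptive ANOVA and the exploratory regressions. What is not stated is any use of them, or of the M.I.N.I., in the gaze contrast.
- **That the Discussion is wrong to say "As the current study focuses exclusively on an ASC population".** Read in context, it means that no other clinical group is enrolled, which is true. It is incomplete as a limitation, because such disorders may also be present inside the ASC group.

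Admitting co-occurring disorders is deliberate and explained, and the ASC sample comes from an existing randomised trial. That is a good reason to leave enrolment alone. An analysis plan that is not shown may add a sensitivity analysis. The eligibility asymmetry, the single named covariate and the Discussion's wording are nevertheless fixed in this document.

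Finally, autistic adults without co-occurring disorder may be less severely affected, so a smaller restricted estimate would not by itself prove confounding. This stands and limits what the remedy can show.

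**Conclusion.** The point holds for attribution, not for the descriptive contrast. The difference between autistic and neurotypical adults, as the protocol defines them, can be estimated as planned. Interpreting that difference as a marker of autism is confounded with co-occurring psychiatric disorder. The protocol describes such disorder as frequent in cases, excludes it in controls and links some forms of it to atypical gaze, but adjusts the gaze contrast for ADHD symptoms only.

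The documents do not fix the size. The 0.09-0.35 SD and the 8%-56% chance of a significant result rest on assumed rates of 30-70%, assumed shifts of 0.3-0.5 SD in the hypothesised direction and no autism effect. Even the largest of these differences is below 0.47 SD, so the figures do not support inferring that co-occurring disorder would explain the whole planned effect. They show only that it could account for a material part.

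**What to change.** Keep enrolment and the main analysis as they are. Before group results are seen:

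1. Pre-specify a supportive analysis of hypotheses 1-2 that compares ASC participants without a current co-occurring M.I.N.I. disorder against the controls, adjusted for age and sex because restriction disturbs the matching.
2. Report its estimate and 95% CI beside the full-sample result, with no pass/fail rule. Half-widths of 0.34-0.41 SD against a planning effect of 0.47 are too wide for a rule on whether the two estimates agree. Adding SIAS or BDI as covariates is only a partial alternative, since controls are likely to overlap little with the ASC group on those scores.
3. Describe the main result as a difference between autistic adults, including those with co-occurring disorders, and adults with no current psychiatric diagnosis.
4. Add to the limitation in the Discussion that the ASC group itself includes participants with such disorders.

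The cost is one analysis on data already collected, plus wording. The restricted estimate is less precise: about 0.34-0.41 SD if 30-70% have a co-occurring disorder (an assumption), against 0.32 SD for the full sample. The report should say that a smaller restricted estimate may reflect milder autism as well as confounding.

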#### Neurotypical participants.

Fifty neurotypical participants will be recruited from the community, using advertisements at relevant institutions or through the websites www.forskningnu.dk and www.forsoegsperson.dk.

Inclusion criteria for the neurotypical group are as follows: (1) age ≥  18 years, (2) ability to give informed consent.

Exclusion criteria for the neurotypical control group are as follows: (1) any current psychiatric diagnoses, including alcohol and drug dependence, (2) an insufficient command of spoken Danish or English. Neurotypical participants will be matched to the ASC sample on age (+/- 2 years) and sex.

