**Methods:**

This case-control study will include 140 adults diagnosed with ASC and 50 neurotypical controls, matched by age and gender. Participants will engage in six VR-based social scenarios, which vary in social complexity and the presence of non-social distractors. Eye information will be measured using eye-tracking technology integrated into a head-mounted display. Gaze behaviour will be analysed through fixation-based metrics on parameters including number of fixations, mean fixation time, and dwell time, on predetermined Areas of Interest.

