### Sample size calculation

Sample size was determined a priori based on one of the primary hypotheses of detecting a between-group difference in total fixation duration (dwell time) on the eye regions. The minimal detectable effect size as set at Hedges’ g =  0.47, as established by Frazier et al.’s 2017 meta-analysis [28]. An allocation ratio of 0.35 was selected due to clinical availability to a cohort of participants with ASC [39] and anticipated greater heterogeneity in gaze behaviour within the ASC group [66].

Assuming a two-sided hypothesis with a significance level of 0.05 and statistical power of 80%, the sample size calculation indicated 139 and 48 NT participants. To account for potential attrition, we will recruit 140 ASC and 50 NT participants.

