### Statistical analyses

Data will be analysed using Statistical Package for the Social Sciences (SPSS) and R software for statistical computing. Data analysis will be conducted using mixed design ANCOVA and MANCOVAs combining between-subjects and within-subjects analysis. Initially, a one-way ANOVA will be performed to examine group differences (ASC vs neurotypical) on demographic, clinical, psychosocial, and social cognitive measures. Means, standard deviations and F-scores will be reported.

To examine gaze behaviour across different regions of interest (social vs non-social areas and regions within these categories), MANCOVAs will be conducted with group (ASC vs neurotypical) as the between-subjects factor and AOIs as within-subjects factors. The potential influence of social complexity will be assessed using a MANCOVA with a group (ASC vs neurotypical) as a between-subject factor and social complexity and AOIs as within-subject factors. ASRS score will be included as a covariate to control for potential confounding influences of ADHD symptomology on visual attention.

Exploratory analyses using linear regression will evaluate potential correlations between eye-movement data and clinical, functional, and social cognitive measures.

All statistical tests for significance will be two-tailed and with a significance level alpha set at p < 0.05. Any missing data will be handled using multiple imputation. In the event of non-normally distributed data, appropriate adjustments will be made, such as using corresponding non-parametric tests.

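### Age and sex are the matching factors for the 50 controls, but the stated group models adjust only for ASRS and include neither

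*Protocol article*

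**What the plan says.** The Design section describes the cases as "including the baseline sample of 140 adults diagnosed with ASC enrolled in a randomised clinical trial" and sets beside them "a neurotypical control group of 50 adult individuals matched on age and sex". The section on neurotypical participants adds a caliper: "Neurotypical participants will be matched to the ASC sample on age (+/- 2 years) and sex". The abstract gives the same two numbers but refers to gender where the Methods refer to sex: "140 adults diagnosed with ASC and 50 neurotypical controls, matched by age and gender".

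The Sample size calculation fixes the imbalance in numbers: "An allocation ratio of 0.35 was selected due to clinical availability to a cohort of participants with ASC". It treats the groups as two independent samples.

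Statistical analyses gives the main models: "MANCOVAs will be conducted with group (ASC vs neurotypical) as the between-subjects factor and AOIs as within-subjects factors". A further model adds social complexity as a within-subject factor. ASRS is the one covariate named, and the reason given is confounding by ADHD symptoms. Age, sex and a matched-set term appear in no stated model. The groups are compared on demographic measures by one-way ANOVA, but no consequence for the gaze models is stated.

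**The concern.** By matching on age and sex, the design identifies them as the confounders to control. The analysis section then adjusts for a confounder, but for a different one. All 140 cases enter the comparison, so what matters is balance between the 50 controls and the whole ASC sample. Closeness of each control to some case is not enough.

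The two groups come from different sources. Cases are the baseline sample of a separate randomised trial, recruited through diagnostic clinics and social support services. Controls answer advertisements and volunteer websites. Every control could lie within 2 years of a case of the same sex while the two groups still differ, for example if controls were matched mainly to early enrolees or to younger cases. A resulting difference in gaze would be read as an effect of ASC, and nothing in the stated models would remove it.

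**Working it through.** **Inputs from the protocol article.** 140 ASC and 50 neurotypical participants; g = 0.47 for dwell time on eye regions; two-sided alpha 0.05; power 80%; ratio 0.35; calculated size 139 and 48.

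**1. The plan's own figure.** The normal approximation for two independent groups gives n(ASC) = (1 + 1/0.35) × ((1.960 + 0.842)/0.47)² = 137.05, that is 138, and 0.35 × 138 = 48.3 controls. With the noncentral t distribution, 139 is the first ASC number to reach 80% at ratio 0.35 (48.65 controls, 80.2%). The stated 139 and 48 are reproduced, as an unmatched, unadjusted two-group comparison.

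**2. When matching suffices.** Simulation under assumed values: case ages 18 + gamma (shape 2, scale 6.5 years), half of each sex, and controls within ±2 years and of the same sex as 50 of the cases. If those 50 are a random subset, the mean imbalance against all 140 is 0 for age (SD 0.115 SD units) and 0 for sex (SD 5.6 percentage points). Matching then protects on average.

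**3. When it does not.** Two adverse scenarios with the same caliper:
- Controls match the first 50 cases, and the later 90 are 5 years older: age imbalance 0.34 SD. Check by hand: the gap is 5 × 90/140 = 3.21 years; the overall SD is √(84.5 + 25 × 50 × 90/140²) = 9.50; 3.21/9.50 = 0.34.
- Younger cases are more likely to be matched (weight falling as exp(−(age − 18)/15)): age imbalance 0.37 SD.

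**4. Bias.** Bias in SD units = age imbalance × age-outcome correlation. The correlation is assumed to be 0.2 to 0.3.
- 0.341 × 0.2 = 0.068 and 0.341 × 0.3 = 0.102
- 0.369 × 0.2 = 0.074 and 0.369 × 0.3 = 0.111

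The range is about 0.07 to 0.11 SD.

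**5. Type I error.** The standard error of the group difference in SD units is √(1/140 + 1/50) = 0.165. With noncentrality = bias/0.165 and 188 degrees of freedom:

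| Bias (SD) | Noncentrality | Two-sided type I error |
|---|---|---|
| 0 | 0 | 5.0% |
| 0.05 | 0.30 | 6.1% |
| 0.10 | 0.61 | 9.3% |

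**6. Cost of adjusting.** Power at 140 and 50 for d = 0.47 (noncentrality 0.47/0.165 = 2.85), with ASRS left out as in the plan's own calculation:

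| Model | df | Power |
|---|---|---|
| Unadjusted | 188 | 81.0% |
| Age and sex, explaining no variance | 186 | 81.0% |
| Age and sex, explaining 5%: d = 0.47/√0.95 = 0.482 | 186 | 82.9% |
| Age and sex, explaining 10%: d = 0.47/√0.90 = 0.495 | 186 | 84.9% |

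The adjusted rows assume balanced groups. With an age imbalance of 0.34 to 0.37 SD, the variance of the adjusted difference grows by the factor 1 + (140 × 50/190²) × imbalance², that is 1.022 to 1.027. Power is then about 80% even if age explains nothing. Adjustment remains cheap when it is most needed.

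**The case against.** **A reader might infer that the matching is impossible**, since one-to-one pairing would leave 140 − 50 = 90 cases without a control. The document does not support this. It nowhere states one-to-one pairing, and one control could serve two or three cases (140/50 = 2.8). The 2-year caliper suggests individual matching but does not establish it.

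**A reader might also infer that the comparison is unprotected.** That goes too far. Matching to a representative set of cases balances age and sex in expectation (step 2), and the planned comparison of demographic measures would bring a clear imbalance to light.

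**Larger biases, such as 0.2 SD from age and sex together, should not be claimed.** They need, for instance, a 5-year age gap and a 15-point sex gap in the same direction. With controls close to 50 of the cases, the other 90 would have to differ from those 50 by 5 × 140/90 = 7.8 years and 15 × 140/90 = 23 points. Strong assumed effects of both factors would be needed as well.

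**An article may leave detail to a fuller document.** This is fair for the matching ratio and reference set, and their absence is not held against the plan. It is also true that the text does not call ASRS the only covariate. But it does specify an adjustment, justifies it by confounding, and does not list the factors that the design itself controls. That is a stated choice that can be judged.

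**The study reaches its power target without adjustment.** This stands: the gain in precision is a benefit, not the repair of a shortfall.

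**Conclusion.** The point holds as an inconsistency between design and analysis that is nearly free to remove. The models as stated leave out both matching factors, so any age or sex imbalance between the 50 controls and all 140 cases would pass uncorrected into the gaze difference. If the controls reflect the whole ASC sample, the expected bias is nil. If they reflect an unrepresentative part, age alone could contribute about 0.07 to 0.11 SD against a planned effect of 0.47; at 0.10 SD, type I error is about 9% in place of 5%. These sizes rest on an assumed age distribution, assumed patterns of selective matching and an assumed age-outcome correlation of 0.2 to 0.3, none of which the document gives. They show what is possible and do not forecast it. The sample size figure is not at fault.

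**What to change.** In Statistical analyses, add age (continuous) and sex as covariates, beside ASRS, in every model that compares ASC with neurotypical participants on gaze, including the social complexity model. Use the variable on which controls were actually matched, and settle on one term, since the abstract says gender and the Methods say sex.

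No new data are needed, because age and sex must be known in order to match. The change is to the wording of the analysis only and leaves recruitment as it is. It costs two degrees of freedom. Power stays at 81.0% with balanced groups, about 80% at the imbalances examined above if the covariates explain nothing, and about 83% to 85% with balanced groups if they explain 5% to 10% of outcome variance.
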